### Home Monitoring

Clinical trials have demonstrated that home spirometry is acceptable to patients with ILD [16-18]. Home spirometry correlates with clinical spirometry and is thought to be effective in detecting disease progression in patients with ILD [19,20]. The widespread increase in societal digitization, including smartphone utilization, has enabled the development of digital care pathways. The COVID-19 pandemic further accelerated the utilization of home monitoring devices, such as pulse oximeters, to support admission avoidance or early discharge from the hospital, shifting the emphasis to supporting the delivery of care closer to home [21,22]. Home monitoring of patients with ILD is not yet part of standard care, despite its perceived utility. This may be due to organizational factors, clinician workload, funding, patient factors including the ability to adopt digital technology, perceived risk to psychological well-being, and concerns regarding the correlation of home and laboratory-based pulmonary function tests (PFTs) [18,23,24].

Home monitoring, including spirometry, pulse oximetry, and patient-reported measures (PRMs), with remote review offers an alternative approach to in-person clinic review and laboratory-based PFTs for patients with ILD. It has the potential to support early identification of disease progression or acute exacerbation, assess response to treatment, enhance QoL, and alleviate health care burden [23]. Evidence of the long-term safety, effectiveness, and acceptability of home monitoring, including assessment of the impact on clinical outcomes, resource use, and patient satisfaction is needed to optimize this approach to patient care. We aim to assess if home monitoring is safe, effective, and acceptable for patients with ILD when offered in addition to standard care. We hypothesize home monitoring will lead to a 50% reduction in routine laboratory-based PFTs and in-person clinic consultations.

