**Figure 1 figure1:**
[figure not shown]
Interstitial lung disease supported self-management schematic. PFTs included FVC, forced expiratory volume, diffusing capacity of the lungs for carbon monoxide, carbon monoxide transfer coefficient, and partial pressure of oxygen in the alveoli. PRMs include idiopathic pulmonary fibrosis patient-reported outcome measure, modified Medical Research Council dyspnea score, EQ-5D-5L, cough visual analogue scale, Global Rate of Change Questionnaire, SpiroQ (home spirometry satisfaction questionnaire), 9-item Patient Health Questionnaire, 7-item General Anxiety Disorder, Porter-Novelli, and modified patient-reported experience measure for patients with rheumatoid arthritis. 6MWT: 6-minute walk test; CPI: composite physiologic index; FVC: forced vital capacity; GAP: gender-age-physiology; HCP: health care professional; HRCT: high-resolution computed tomography; MDT: multidisciplinary team; PFT: pulmonary function test; PRM: patient-reported measure.

The registering clinician will be responsible for setting thresholds for a ≥10% decline in absolute forced vital capacity (FVC) and oxygen saturation <94%, according to the individual’s baseline measurement [34]. If measurements fall below the threshold, alerts will be sent to the clinical team via the browser-based portal. The clinical team will review daily alerts during weekday working hours (Monday to Friday, 9 AM-5 PM). Each review will consider measurements, quality of the measurements, trends, changes from baseline, and contributing factors. Patients may require follow-up telephone or in-person clinic assessment to guide management decisions, for example, with repeat high-resolution computed tomography (HRCT), 6-minute walk test, long-term oxygen therapy assessment, and laboratory-based PFTs. Patients will continue to receive standard care as per their local clinical protocols.

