### Variables

The variables to be measured and how they will be measured are outlined in Table 1.

**Table 1 table1:** Outcome measures.

		Measurement tools

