**Primary outcome measures**		
	Potential to detect disease progression, acute exacerbation, or response to treatments enabling prompt review of patients and access to appropriate therapies compared with standard care	Browser-based portal: Number of patients with ≥5%-10% decline in FVC^a^ Time to ≥5%-10% decline in FVC Number of patients diagnosed with progressive pulmonary fibrosis who become eligible for antifibrotic treatment PRM^b^ changes in score Number of patients who start or change their prescription for oxygen therapy Time to titrate or start oxygen therapy Electronic case report form: Number of acute exacerbations and how they were managed Interventions made (type and number)
	Impact on the number of in-person clinic consultations with ILD^c^ clinicians compared with standard care	Electronic case report form: (data comparison with 2019 to 2020): Number of F2F^d^ consultations Number of telephone consultations Number of video consultations
	Impact on the number of laboratory-based pulmonary function tests compared with standard care	Electronic case report form (data comparison with 2019 to 2020): Number of F2F consultations Number of telephone consultations Number of video consultations
	Real-world patient acceptability of home monitoring program, including spirometry, oximetry, and PRMs	Browser-based portal: Frequency of patient recording of key measurements (eg, spirometry, pulse oximetry, PRMs) Duration (minutes) of regular patient engagement with the application Patient engagement and experience measure ratings Electronic case report form: Patients not eligible or declined participation and reason

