### Quantitative Variables

Statistical analysis will include patient demographic data, including age, gender, ethnic background, smoking status, occupation and geographical location, measurements and PRM responses, number and type of alerts and interventions, number and mode of clinic consultations, and investigations.

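### Table 1 gives the primary outcome on laboratory pulmonary function tests the consultation counts of the row above, so the PFT part of the 50% hypothesis has no stated measure there

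*Protocol article*

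**What the plan says.** The Variables section of the protocol article makes Table 1 the place where measurement is defined: "The variables to be measured and how they will be measured are outlined in Table 1".

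The second primary outcome in that table is "Impact on the number of in-person clinic consultations with ILD^c^ clinicians compared with standard care", with counts of face-to-face, telephone and video consultations as its tools. The third is "Impact on the number of laboratory-based pulmonary function tests compared with standard care". Its tools cell reads "Electronic case report form (data comparison with 2019 to 2020): Number of F2F consultations Number of telephone consultations Number of video consultations".

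The Home Monitoring section of the Introduction states the hypothesis: "We hypothesize home monitoring will lead to a 50% reduction in routine laboratory-based PFTs and in-person clinic consultations". The Conclusions paragraph of the Abstract repeats it.

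Two other places touch on PFT data. Quantitative Variables says the analysis will include "number and mode of clinic consultations, and investigations". The Study Design text after Figure 1 lists the assessments that may follow an alert, among them "6-minute walk test, long-term oxygen therapy assessment, and laboratory-based PFTs".

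**The concern.** The label of the third primary outcome and its measures do not match. The label names laboratory tests; the measures are consultation counts, identical in content to those of the second outcome. An analyst who followed Table 1 literally would report consultations under a heading about PFTs.

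The PFT outcome carries one of the two quantities in the study's only numerical hypothesis. Consultation counts cannot stand in for it. The plan adds virtual reviews every 3 months and lets alerts lead to laboratory tests, so the number of in-person visits and the number of laboratory tests need not move together. The Results section says data analysis is already under way. A PFT count whose definition is settled only now, with data in view, would leave this outcome open to choices made after the fact.

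**Working it through.** The plan gives no figure to reproduce here. The check is a comparison of cells, then a search of the article for any other PFT count.

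**Step 1: the two rows side by side (Table 1, primary outcomes)**

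| | In-person consultations (row 2) | Laboratory PFTs (row 3) |
|---|---|---|
| Source | Electronic case report form | Electronic case report form |
| Comparison | 2019 to 2020 | 2019 to 2020 |
| Tool 1 | Face-to-face count | Face-to-face count |
| Tool 2 | Telephone count | Telephone count |
| Tool 3 | Video count | Video count |

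In row 3, 3 of 3 tools match row 2 and 0 of 3 count a PFT.

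**Step 2: is this an artefact of text extraction?** The two cells differ in small ways. Row 2 has an extra colon after the name of the form and a footnote mark on the face-to-face abbreviation; row 3 has neither. A program that repeated a cell would be expected to repeat it exactly. Row 3 therefore appears to be text in the article itself.

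**Step 3: the other rows of Table 1.** There are 4 primary and 7 secondary outcomes, 4 + 7 = 11 rows. None lists a count of laboratory PFTs. The first primary row records the type and number of interventions and declines in FVC from the browser-based portal; neither is a count of laboratory tests. The secondary row on access to specialised services counts interactions with the ILD team, which is again not a count of tests.

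**Step 4: the hypothesis against the table.** It has two components. In-person consultations have a matching measure (row 2). Routine laboratory PFTs have none. So 1 of 2 components lacks a measure in Table 1.

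**Step 5: the rest of the article.** Quantitative Variables mentions investigations, and Study Design treats laboratory PFTs as one possible assessment after an alert. Neither names a PFT count per patient, separates routine from triggered tests, or links PFTs to 2019 to 2020.

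**Step 6: what the row 3 tools would show (hypothetical).** Table 1 gives 3-4 contacts a year as an example of standard care. Assume 4 in-person visits and 4 routine laboratory tests in the comparison year, and 2 in-person visits in the monitored year.

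- Fall in face-to-face count: (4 − 2)/4 = 50%.
- If routine tests stay at 4: (4 − 4)/4 = 0%.
- If routine tests drop to 2: (4 − 2)/4 = 50%.

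The face-to-face count reads 50% in both cases, so it cannot tell a halving of routine tests from no change. The number of tests and the monitored-year visits are assumed only to show this.

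**The case against.** The strongest reply is that this is a slip in one cell of a condensed article. The row label is itself a count of PFTs, the hypothesis names PFTs, and nobody would plan to measure tests by consultations. A copy error is the likelier explanation, though the article does not say so.

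A reader might go further and infer that PFTs are never counted and that half of the hypothesis cannot be tested. The documents do not support that. Investigations are included in the planned analysis, and laboratory PFTs are named as an assessment that may follow an alert, so the data may well be collected. The case report form is not shown and may already hold a PFT field. Nor is it right to call the third outcome a duplicate of the second: the outcomes differ, and only their tools cells agree.

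It is also fair to say that an alert-triggered test is not routine. A rise in triggered tests would bear on the row 3 label, which covers all laboratory PFTs, but would not by itself contradict the hypothesis about routine ones.

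What stands is the mismatch. This is not detail left to a fuller document: the article states a measure for a primary outcome, and it is the wrong variable. The general reference to investigations does not correct it.

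**Conclusion.** The point holds in a limited form. As Table 1 specifies it, the third of four primary outcomes does not measure laboratory PFTs, and the PFT component of the 50% hypothesis has no stated measure in that table. This is an internal inconsistency between a label and its tools. It needs correction because it affects a primary outcome and the only quantified claim.

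The conclusion rests on the article's own statement that Table 1 sets out how variables are measured. It does not establish that PFT data are absent or that the hypothesis is untestable; both depend on a case report form and hospital records that are not shown. No sample size or power figure changes, because the planned 200 patients are described under Study Size as a pragmatic number.

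**What to change.** Replace the row 3 tools in Table 1 with: number of laboratory-based PFTs per patient over the 12 monitored months, and over the same length of time in the 2019 to 2020 comparison period, taken from the same source in both. Count routine tests separately from alert- or symptom-triggered tests. The hypothesis concerns routine PFTs, while the row label covers all laboratory PFTs, and the split serves both.

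Then check the case report form. If it already holds these counts, only the table needs correcting. If it does not, extract PFT dates, and whether each test was routine or triggered, from hospital records for both periods before the analysis closes. This assumes that the two Trusts hold such records in retrievable form, which the article does not state.

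The cost is a one-row correction and, at most, a small amount of retrospective data extraction. Recruitment, follow-up and sample size are unaffected.

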**Conclusions:**

We hypothesize home monitoring will be safe, effective and acceptable for patients with ILD and result in a 50% reduction in routine laboratory-based pulmonary function tests and in-person clinic consultations.

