## Results

This study was funded by NHS Digital in September 2021. Patient recruitment and data collection started in March 2022. By January 2024, we recruited 186 patients. All patients will have home monitoring for at least 12 months. Data analysis is ongoing, and results are expected to be published at the end of 2025. No significant safety concerns are anticipated with any measurements carried out as part of this study. In the case of adverse events, the established clinical safety procedures, investigation protocols, and reporting guidelines for each Trust will be adhered to, ensuring thorough and consistent management in accordance with established guidelines. The approach to care outlined in this protocol signifies a potentially pivotal moment in the transformation of health care delivery to patients with ILD.

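### The primary outcome on laboratory PFTs is given only consultation counts as its measures, and the 50% hypothesis covers routine PFTs while the outcome label covers all of them

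*Protocol article*

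**What the plan says.** The Variables section of the protocol article refers the reader to Table 1 for what is measured and by what means. Among the primary outcomes, one row is labelled "Impact on the number of laboratory-based pulmonary function tests compared with standard care". The measurement tools in that row are "Electronic case report form (data comparison with 2019 to 2020): Number of F2F consultations Number of telephone consultations Number of video consultations". The row above, on in-person consultations, lists the same three counts against the same comparison period.

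The quantified aim appears twice. The Home Monitoring section of the Introduction says "We hypothesize home monitoring will lead to a 50% reduction in routine laboratory-based PFTs and in-person clinic consultations". The Abstract's Conclusions expect home monitoring to be "safe, effective and acceptable for patients with ILD and result in a 50% reduction in routine laboratory-based pulmonary function tests", with in-person consultations included in the same sentence. Both attach the word routine to the PFTs.

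Study Design allows an alert to lead to a telephone call or a visit in person, and the examples it gives of the ensuing work-up are "with repeat high-resolution computed tomography (HRCT), 6-minute walk test, long-term oxygen therapy assessment, and laboratory-based PFTs". Quantitative Variables includes in the analysis "number and type of alerts and interventions, number and mode of clinic consultations, and investigations". On timing, the Results section says "Data analysis is ongoing, and results are expected to be published at the end of 2025".

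**The concern.** There are two linked problems.

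- **The measure does not match the outcome.** A primary outcome about PFTs is defined by counts of consultations. An analyst who follows the table would report consultations twice and PFTs not at all. This is not detail left to a fuller document: the article fills the cell, but with the measures of a different outcome.
- **Two PFT counts are in play.** The hypothesis is about routine PFTs, whereas the outcome label takes in every laboratory PFT. The programme can remove scheduled tests and, through alerts, add unscheduled ones. If only the routine count is reported, tests generated by the programme drop out of sight.

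What is at stake is half of the one numerical claim in the article. With analysis already in progress, the count should be fixed in writing before the result is presented.

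**Working it through.** The article gives no calculation behind the 50% and no PFT rate, so there is no figure to reproduce. The check is a comparison of texts plus one identity.

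**Step 1: the two adjacent primary outcome rows in Table 1.**

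| Row | Outcome | Measures listed | PFT counts among them |
|---|---|---|---|
| Consultations | In-person clinic consultations | Face-to-face, telephone, video consultations | 0 of 3 (none needed) |
| PFTs | Laboratory PFTs | Face-to-face, telephone, video consultations | 0 of 3 |

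No other row of Table 1 contains a count of laboratory PFTs. The FVC items in the first primary outcome row are drawn from the home-monitoring portal and concern decline, not the number of laboratory tests.

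**Step 2: does other text supply the measure?** Quantitative Variables names investigations in general. The Figure 1 caption lists which lung function quantities a PFT includes. Both suggest that PFT data exist. Neither says that the number of PFTs is the outcome measure, separates routine from triggered tests, or links a PFT count to 2019 to 2020.

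**Step 3: routine against all.** Per patient-year, let r0 be routine PFTs in 2019 to 2020, u0 unscheduled PFTs in that period, and u1 unscheduled PFTs during home monitoring. Suppose routine PFTs halve exactly as hypothesized. Then

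fall in all PFTs = 1 − (0.5 × r0 + u1) / (r0 + u0).

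This equals 50% only when u1 = u0 / 2. If u1 is larger, the total falls by less than 50%; if smaller, by more. The result needs no assumed rate.

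**Step 4: illustration, on assumed rates only.** The Abstract describes visits every 3 to 6 months. Assume one routine PFT per visit, so r0 = 12/6 = 2 to 12/3 = 4. Assume u0 = 0.5.

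| u1 (assumed) | Fall in all PFTs, r0 = 2 | Fall in all PFTs, r0 = 4 |
|---|---|---|
| 0 | 1 − 1/2.5 = 60% | 1 − 2/4.5 = 55.6% |
| 0.25 | 1 − 1.25/2.5 = 50% | 1 − 2.25/4.5 = 50% |
| 0.5 | 1 − 1.5/2.5 = 40% | 1 − 2.5/4.5 = 44.4% |
| 1 | 1 − 2/2.5 = 20% | 1 − 3/4.5 = 33.3% |

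The answer moves with u0. With u0 = 0 and u1 = 0.5, the fall is 1 − 1.5/2 = 25% (r0 = 2) to 1 − 2.5/4 = 37.5% (r0 = 4). The figures show only that the two counts can give different answers to a 50% claim. They do not estimate what happens in this study.

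**The case against.** The best defence is that this is a copying slip in one cell of a condensed article. The label itself names a countable quantity, the row names its comparison period, and investigations are among the analysed data. That is probably how the error arose, and a reader who inferred that no PFT data will be available would go beyond the text. It does not repair the row: the article's own definition of the measure is still wrong for a primary outcome.

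Could the repetition come from reading the PDF? The two cells are punctuated differently (a colon follows the word form in the consultation row but not in the PFT row), which points to separately typed cells. This evidence is modest. The missing footnote mark on the face-to-face abbreviation adds nothing, because the table marks abbreviations only at first use.

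On routine against all, a hypothesis about a subset can properly sit beside a broader outcome, and both statements of the 50% say routine. That stands. A reader might infer a contradiction, or conclude that the 50% should be moved to all PFTs; the documents support neither. Changing the target while analysis is under way would be a preference imposed late. What remains is that alerts can generate laboratory PFTs, so the routine count alone may give an incomplete picture.

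Two further inferences are also not supported. Offering home monitoring on top of standard care does not rule out a fall in visits or PFTs, since the article describes follow-up frequency as flexible and remote review as an alternative. The yearly contact benchmark for the secondary access outcome is offered only as an example, with 2019 to 2020 named beside it.

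**Conclusion.** The point holds as a minor one. As printed, the PFT row lists three measures, all consultations, and so does not measure its own primary outcome. This rests on the text alone and needs no assumption.

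The second part is smaller and conditional: if routine PFTs halve, the fall in all PFTs is below 50% whenever unscheduled PFTs do not also at least halve. Whether that happens here cannot be told from the article. The percentages in the illustration depend wholly on assumed rates and should not be cited as the size of any bias. The finding is a wrong measure in one cell and an incomplete count, not an absence of PFT data and not a conflict between hypothesis and outcome.

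**What to change.** 1. In the PFT row of Table 1, replace the three consultation counts with the number of laboratory PFTs per patient-year, in total and split into routine and unscheduled or alert-triggered, compared with the same counts for 2019 to 2020.
2. Keep the 50% hypothesis on routine PFTs as stated, and report the change in all PFTs beside it.

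No new patients, visits or tests are needed. The cost lies in record review: unscheduled PFTs must be identified by one rule in both periods, and alerts did not exist in the earlier one, so there the split is simply routine against unscheduled. The total reduction may look less favourable than the routine one, and the comparison stays historical.

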**Secondary outcome measures**		
	Impact on clinician time and experience compared to standard care	Browser-based portal: Clinician time spent on the browser-based portal Electronic case report form: Time taken to address each alert
	Correlation of PRMs with patient symptoms	Electronic case report form: Review symptoms and measurements every 3 months
	Number of patient requests for technical support	Browser-based portal: Number and length of unique interactions with the technical team
	Impact on the number of ILD-related hospital admissions and duration of inpatient stay	Electronic case report form: Review admissions every 3 months
	Impact on patient access to ILD specialized services	Browser-based portal: Completion of PRMs Electronic case report form (data comparison with defined standard care, eg, 3-4 per year, and 2019 to 2020): Number of interactions with the ILD team
	Correlation between home monitoring and patient satisfaction	Browser-based portal: PRMs Duration and frequency of patient app use
	Impact on travel costs to the patient, NHS^e^, and environment	Electronic case report form: Postcode and usual mode of travel at registration Cost of mode of transport (car mileage 45p per mile) Dependent on carer support

^a^FVC: forced vital capacity.

^b^PRM: patient-reported measure.

^c^ILD: interstitial lung disease.

^d^F2F: face-to-face.

^e^NHS: National Health Service.

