## Abstract

**Background:**

Interstitial lung diseases (ILDs), a group of parenchymal lung disorders, present with varying degrees of inflammation and fibrosis, which lead to symptoms such as progressive breathlessness, impaired quality of life (QoL), and reduced life expectancy. Patients with ILD can experience a sudden worsening of their condition, known as an acute exacerbation, which is associated with inappropriate hospital admissions, concomitant National Health Service (NHS) costs, impaired QoL, and high mortality. The heterogeneity of ILDs, the unpredictability of acute exacerbations, and significant variation in disease progression and response to treatment present numerous management challenges. Standard care typically involves 3-6 monthly hospital outpatient visits to monitor disease and assess response to treatment. Home monitoring with remote review of spirometry, pulse oximetry, and patient-reported measures offers an alternative approach to in-person clinic review and laboratory-based physiological measurements. Clinical trials indicate home monitoring of patients with ILD is acceptable, and results correlate with laboratory-based pulmonary function tests (PFTs). The impact of implementing home monitoring for patients with ILD in a real-world setting is not well understood.

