### Participants

A total of 200 patients will be recruited from 2 ILD specialist services in the United Kingdom to achieve robust and comprehensive insights from a diverse patient population. Adhering to the inclusion and exclusion criteria, ILD specialist clinicians will recruit adults aged 18 years and older, with a tertiary center multidisciplinary diagnosis of ILD confirmed by HRCT and expectation of variability in progression. Patients will need to be able to perform spirometry and achieve a baseline FVC >45% predicted value within 6 months of recruitment. They will need access and the ability to use a smart device with internet and email. A budget will be available to provide smart devices and internet connectivity to patients who do not have access. Patients will need to be able to communicate with the team, understand written instructions, and complete PRMs. Patients will not be able to participate if they have a life expectancy of less than 6 months determined by clinical judgment, contraindications to spirometry as per Association for Respiratory Technology and Physiology guidelines, upper or lower respiratory tract infection within 4 weeks, acute exacerbation within 4 weeks, and active cancer diagnosis or life-limiting malignancy [36].

All patients will have 3 monthly virtual reviews with an ILD specialist clinician. Home monitoring measurements will be reviewed. Patients will be asked to report any upper or lower respiratory tract infections, acute exacerbations, accident and emergency presentations, or hospital admissions in the previous 3 months. Responses will be documented on the browser-based portal and electronic case report form. Daily alerts will be reviewed and addressed by the clinical team. Alert management will be documented on the browser-based portal and electronic case report form. Patients who miss weekly measurements for 3 weeks or choose to withdraw from home monitoring will be contacted, and the reason for stopping will be documented on the browser-based portal.

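### The access outcome counts all ILD-team interactions, and the protocol's own four scheduled reviews a year push that count to or above its comparators

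*Protocol article*

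**What the plan says.** In the protocol article, Table 1 (Secondary outcome measures) lists the outcome "Impact on patient access to ILD specialized services". It has two measures. From the portal, it takes "Completion of PRMs". From the electronic case report form (eCRF), it takes a contact count with two comparators: "data comparison with defined standard care, eg, 3-4 per year, and 2019 to 2020): Number of interactions with the ILD team". The row does not define an interaction and excludes no type of contact.

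Three other places bear on that count:

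- Participants: "All patients will have 3 monthly virtual reviews with an ILD specialist clinician". The interval is every 3 months, since at each review patients report events such as "accident and emergency presentations, or hospital admissions in the previous 3 months". The same section says that patients who miss readings for three weeks will be contacted.
- Study Design, text under Figure 1: "Patients will continue to receive standard care as per their local clinical protocols". Alerts may also lead to telephone or in-person assessment.
- Abstract, Background: "Standard care typically involves 3-6 monthly hospital outpatient visits to monitor disease and assess response to treatment".

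The Abstract and the Home Monitoring section hypothesize that in-person consultations will fall by half.

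**The concern.** An access measure should tell us whether patients reach the specialist team more readily because they are monitored at home. Here the count includes contacts that the protocol books for everyone, whatever happens to the patient and however easy or hard it is to reach the team. Four booked reviews already equal the top of the benchmark. Any retained clinic visit, alert call or call about missed readings comes on top.

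If the total is then read as better access, the report would present the study's visit schedule as a benefit. This is a secondary outcome, but the Principal Findings section expects the results to support adoption, guidelines and policy decisions, where a statement about access would carry weight.

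There is also a smaller inconsistency. The benchmark in Table 1 and the description of standard care in the Abstract do not give the same yearly frequency.

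**Working it through.** **Inputs**

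- Benchmark: 3 to 4 interactions a year (Table 1, given as an example), plus 2019 to 2020 data. The article gives no counts for 2019 to 2020.
- Scheduled reviews: every 3 months (Participants).
- Standard care: visits every 3 to 6 months (Abstract), continuing during the study (Study Design).
- Hypothesized cut in in-person consultations: 50% (Home Monitoring).
- Follow-up: 12 months (Setting).

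**Step 1: the benchmark.** Contacts per year = 12 / interval in months. Visits every 3 to 6 months give 12/6 = 2 to 12/3 = 4 a year. Table 1 gives 3 to 4. The upper ends agree and the lower ends do not (2 against 3). Three a year would be a 4-month interval.

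**Step 2: the count under the protocol.** Scheduled reviews: 12/3 = 4 a year. Let *s* be standard visits a year (2 to 4) and *f* the share retained. For a patient who attends every review, and before any alert or missed-reading contact:

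count = 4 + *f* × *s*

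| Standard visits retained | *s* = 2 | *s* = 4 | Position against 3 to 4 |
|---|---|---|---|
| None (*f* = 0) | 4 | 4 | at the top |
| Half (*f* = 0.5) | 5 | 6 | above |
| All (*f* = 1) | 6 | 8 | above |

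**Step 3: the 2019 to 2020 comparator.** Assume a patient's past contacts equalled the standard visits, 2 to 4 a year. The ratio of study count to past count is (4 + *f* × *s*) / *s*:

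| Standard visits retained | *s* = 2 | *s* = 4 |
|---|---|---|
| None | 4/2 = 2.0 | 4/4 = 1.0 |
| Half | 5/2 = 2.5 | 6/4 = 1.5 |
| All | 6/2 = 3.0 | 8/4 = 2.0 |

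No ratio is below 1. If past contacts were more frequent than assumed, the study count falls below the past count only when 4 + *f* × *s* < *s*, that is, when *s* > 4 / (1 − *f*). With half retained, this needs more than 4/0.5 = 8 past visits a year. With none retained, it needs more than 4.

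**Step 4: missed reviews.** If no standard visit is retained, a patient must attend 3 of the 4 reviews to reach 3 contacts, and all 4 to reach 4. With half of two visits retained (1 visit), 2 of 4 reviews reach 3 contacts and 3 of 4 reach 4. Non-attendance can therefore pull a count below the benchmark.

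**Step 5: the count without scheduled reviews.** What remains is *f* × *s*: 2 to 4 with full standard care or 1 to 2 with the 50% cut, plus alert-driven and patient-initiated contacts. The size of those last two is not fixed by the schedule, so the study can inform it.

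**The case against.** The strongest reply is that the scheduled reviews belong to the intervention. The article describes home monitoring with remote review as an alternative to clinic attendance, and home measurements are discussed at these reviews. On that reading, four more specialist contacts are part of what the programme does for access. This stands far enough that the reviews should not be dropped from the report. It does not make the total interpretable: a rise that the protocol books in advance describes what was delivered, and it has to be kept apart from contacts that arise from need.

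A reader might infer that the outcome is met by construction or can only come out favourable. The document does not support this. Table 1 sets no threshold and no direction, Statistical Methods summarizes all end points descriptively, and missed reviews, death or withdrawal can lower a count.

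A reader might also take 6 to 8 contacts a year as a minimum. It is not. It assumes that all standard visits are kept, while the study hypothesizes that in-person visits will halve. The floor for full attendance is 4.

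On the benchmark, Table 1 gives an example for interactions, whereas the Abstract describes typical outpatient visits. The ranges overlap, and a fuller definition may exist in the full protocol. The discrepancy is therefore limited to the lower end, but it still needs one consistent statement.

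Finally, the article does not say who contacts patients with missed readings, or that such a contact counts as an interaction with the ILD team. Counting it is a plausible reading of an undefined term.

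**Conclusion.** The point holds as a problem of interpretation. With full attendance, the protocol alone yields 4 contacts a year if all standard visits are replaced, 5 to 6 under the hypothesized cut and 6 to 8 with standard care in full, against a benchmark of 3 to 4. Against an assumed past of 2 to 4 visits a year, the count is 1.0 to 3.0 times the past figure. The total is driven towards equal or more contacts by the schedule and cannot by itself show improved access.

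This rests on three assumptions: that the virtual reviews count as interactions (the natural reading, since they are with a specialist clinician, but not stated), that four reviews fall within the 12 months, and that past contacts were near the standard frequency. PRM completion does not repair the measure. It reflects use of the app, and Table 1 already lists the frequency of PRM recording under acceptability.

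The disagreement between 3 to 4 and 2 to 4 a year is real but small. Which figure is right is for the authors to state.

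**What to change.** In the access row of Table 1:

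1. Report protocol-scheduled reviews and missed-reading contacts separately from alert-driven and patient-initiated contacts.
2. Base any statement about access on the unscheduled contacts and on the time to address each alert, which Table 1 already collects. That item sits under clinician time, so say whether it means elapsed time to response or effort spent.
3. State that the total count is descriptive and will not be interpreted as improved access against either comparator.
4. Reconcile the standard-care frequency between Table 1 and the Abstract.
5. Keep PRM completion under acceptability only.

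The cost is mainly classification. Alert management and the 3-monthly reviews are already documented in the portal and eCRF. The article does not say that patient-initiated contacts are flagged, so some may have to be identified from the records. With 186 patients recruited by January 2024, much of this will be retrospective, but the Results section says that analysis is still ongoing. The access result may look less favourable.
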